### Ethics Approval

The study protocol was approved by the Institutional Ethics Committee at Madras Diabetes Research Foundation, All India Institute of Medical Sciences, and the Human Research Ethics Committee at Deakin University, Australia. Consent is obtained from all participants. At baseline testing, all participants were also given a plain language statement of the study.

#### Statistical Analysis

Quantitative analyses of the obtained data will be conducted in STATA (StataCorp, Version 15, College Station, Texas) and SPSS (IBM SPSS Statistics for Windows, Version 24.0. Armonk, NY). A probability of <0.05 will be considered statistically significant for all tests. Effectiveness of the intervention will be assessed by measuring the differences in the study arms in terms of the primary outcome, weight loss and secondary outcomes, behavioral and social variables, and cost-effectiveness. Continuous variables will be assessed for normality, and anomalous values will be categorized. All variables will undergo descriptive analyses. *t* tests will be used to compare between the 2 groups. Data will be presented before and after adjusting for confounders. Qualitative data include analyses of the audiotaped transcripts from the FGDs. The transcripts will be de-identified, and textual data will be extracted from the same. Following this, key themes will be identified and reported.

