**Results:**

The study outcomes are weight loss (primary measure of effectiveness); improvement in cardiometabolic risk factors (ie, waist circumference, blood pressure, glucose, insulin, and lipids); and improvement in physical activity, quality of life, and dietary habits. Sustainability will be assessed through focus group discussions.

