#### Program Acceptability

Program acceptability is assessed through focus group discussions (FGDs) with the intervention group participants at the end of follow-up. We plan to organize 2 FGDs at each site consisting of at least eight participants each. Thus, a total of 6 FGDs will be conducted in the study. The participants will be encouraged to share their experience on the benefits and problems of the intervention, financial worth of the program, and suggestions, if any, for improvement. Participants who drop out will also be contacted to understand their reasons for dropping out and to obtain their feedback.

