#### Sample Size Calculation

Our study randomizes 1500 individuals across 3 sites to receive either the mHealth diabetes prevention program or usual care with a 6-month maintenance period. Considering an obesity prevalence of 20% as reported in the Indian Council of Medical Research-India Diabetes (ICMR-INDIAB) study [38,39] and with south Asians having a low BMI threshold compared with the rest of the population, 5% weight loss was determined as the primary outcome in the intervention group. On the basis of this assumption, a sample size of 588 individuals in each arm will be required to obtain a minimum of 3% difference in weight loss between groups with a power of 80% and a significance level of 5%. As this is a mobile phone–based intervention study, expecting a slightly higher dropout rate of 25%, 735 individuals in each group will need to be tested in the trial, resulting in a total of 1470, which has been rounded off to a total of 1500 individuals across 3 sites (500 per site).

All sample size and power calculations were done using the OpenEpi (The OpenEpi Project, Version 3, Atlanta, Georgia).

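### Replace t tests shown before and after adjustment for unnamed confounders with one named primary analysis, adjusted for baseline value and site

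*Protocol article*

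**What the plan says.** The Statistical Analysis section of the protocol article names one between-arm method, the t test, and then two presentations of the result: t "tests will be used to compare between the 2 groups. Data will be presented before and after adjusting for confounders". It lists no confounders and does not say which presentation decides the trial.

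The endpoint is described in two ways. The Results paragraph of the Abstract says "The study outcomes are weight loss (primary measure of effectiveness". Sample Size Calculation says "5% weight loss was determined as the primary outcome in the intervention group", and sizes the trial "to obtain a minimum of 3% difference in weight loss between groups with a power of 80% and a significance level of 5" per cent.

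Table 1 and the Data Collection section have weight measured at baseline, post intervention and end of follow-up. Most secondary measures follow the same schedule. In Table 1 the 2-hour glucose is taken only at baseline and end of follow-up.

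On dropout, Sample Size Calculation inflates the sample, "expecting a slightly higher dropout rate of 25" per cent. Program Acceptability adds: "Participants who drop out will also be contacted to understand their reasons for dropping out". The article gives no rule for analysing people without a final weight.

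**The concern.** Three features of the stated method can be improved with data the trial already collects.

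- **Two results, no primary.** After randomisation, baseline differences between arms arise by chance, so there are no confounders to identify. What is needed is a short list of prognostic covariates fixed beforehand. An open list with two co-equal results leaves room for choice once data are seen. The Randomization section says that site teams and participants know the allocation, which makes fixing the choice more important.
- **Inefficient use of baseline.** A t test on change subtracts the baseline value with a coefficient of exactly 1. Regression on baseline estimates the coefficient and is at least as precise in large samples.
- **One visit at a time.** A t test at the final visit makes no use of the 3-month weight of someone who later leaves. If people with poor early loss leave one arm more than the other, the final-visit comparison of those still present is biased. The early weights carry information that can correct this.

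**Working it through.** **1. The plan's own figure.** Inputs from Sample Size Calculation: a 3-point difference, 80% power, 5% significance (taken as two-sided) and 588 per arm. Reading the 5% as a proportion in the intervention arm, against 2% in control, the mean proportion is 0.035:

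n = [1.960 × √(2 × 0.035 × 0.965) + 0.842 × √(0.05 × 0.95 + 0.02 × 0.98)]² / 0.03² = (0.5094 + 0.2180)² / 0.0009 = 587.9, so 588.

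This matches exactly. As a difference in mean percent weight change, 588 per arm would need an SD of 3 / (2.802 × √(2/588)) = 18.4 points. With an assumed SD of 3 to 6 points, 16 to 63 per arm would be enough for a 3-point difference. The sample size therefore matches a binary endpoint, while the t test implies a continuous one.

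**2. Gain from baseline adjustment.** With equal variances at both visits and correlation ρ, the variance of a change score is proportional to 2(1−ρ), and that of the baseline-adjusted comparison to 1−ρ². Their ratio is (1+ρ)/2. The article gives no correlations, so these are assumed.

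| Outcome | ρ | (1+ρ)/2 | Variance reduction |
|---|---|---|---|
| Weight | 0.97 | 0.985 | 1.5% |
| Weight | 0.95 | 0.975 | 2.5% |
| Weight | 0.90 | 0.95 | 5% |
| Secondary outcomes | 0.7 | 0.85 | 15% |
| Secondary outcomes | 0.6 | 0.80 | 20% |
| Secondary outcomes | 0.5 | 0.75 | 25% |
| Secondary outcomes | 0.4 | 0.70 | 30% |

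**3. Cost of choosing between two results.** Suppose there is no true effect, 562 per arm are analysed (750 × 0.75), and whichever version has p < 0.05 is reported. Simulation (6,000 trials per setting) gave type I error of 6.0%, 6.4%, 7.4% and 8.2% when the covariates explain 2%, 10%, 30% and 50% of the outcome variance. As a check, the two test statistics have correlation of about √(1−R²). The bivariate normal probability that at least one exceeds 1.96 in size is then 5.7%, 6.5%, 7.6% and 8.3%, which agrees within simulation error.

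**4. Use of the 3-month weight.** Simulation assumptions: 750 per arm, 3-month weight known for everyone, SD 5 points, correlation 0.7 between the two follow-up visits, and about 25% missing the final weight.

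- *Missing at random, unrelated to response:* both methods are unbiased. The standard error is 0.300 for the t test and 0.283 for the likelihood estimate using both visits, about 6% smaller.
- *Deliberately strong mechanism:* in the intervention arm only, the log-odds of leaving rise by 0.25 for each point less lost at 3 months. With no true effect, the t test on those present shows a difference of 0.95 points and rejects in about 90% of trials. The estimate using both visits shows about 0 and rejects in about 5%.

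**5. Scale of a return-to-baseline sensitivity analysis.** Assume completers lose 3% and 1%, a difference of 2.0 points. If those who leave are set back to baseline, the difference is 0.75 × 3 − 0.75 × 1 = 1.5 with 25% dropout in each arm, or 0.70 × 3 − 0.80 × 1 = 1.3 with 30% against 20%. This measures that imputation, not the repeated-measures model.

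**The case against.** The strongest reply is that the article is condensed and the criticism reads too much into its silence. Much of that reply stands.

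- **Baseline and site.** A reader might infer that the plan ignores both. It does not say so. Weight loss already subtracts baseline, and the unnamed adjustment set may include baseline weight and site. Leaving out site costs precision and does not bias a randomised comparison with arms near balance within site.
- **Large precision gains.** A variance reduction of 80 to 94% for weight can be derived from 1−ρ² at correlations of 0.90 to 0.97. It requires a t test on raw follow-up weight, which conflicts with an outcome of weight loss.
- **Dropouts excluded.** A reader might infer that 25% of participants are to be dropped. No section states a completers-only rule, and missing-data handling may sit in a fuller document. That such exclusion would favour the intervention is also unsupported: step 4 shows no bias when dropout is unrelated to response.
- **A natural main result.** The t test can be read as the main comparison and the adjusted version as supportive, and showing both is common practice. Nothing says that covariates will be chosen after seeing the data.

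What the reply does not meet is that the stated sentence names no primary version and no covariates, and relies on a test less efficient than one the collected data allow.

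**Conclusion.** The point holds as an improvement to a stated method. The article fixes t tests with two presentations, names no covariates and designates neither result primary. One prespecified model is better and costs almost nothing.

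The gain is small for weight (1.5 to 5% of variance) and moderate for secondary outcomes (15 to 30%), under the assumed correlations. The type I error cost of roughly 1 to 3 percentage points arises only if the choice between versions is made after seeing results. The benefit with dropout ranges from a standard error about 6% smaller to removal of a bias near 1 point. The upper end depends on a strong, arm-specific mechanism that the documents do not establish. Dropout therefore supports the choice of model and is not an error in its own right.

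**What to change.** Replace the t-test and confounder sentences with text along these lines:

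*The primary analysis is a mixed model for repeated measures of percent weight change at post intervention and end of follow-up, in participants as randomised, with arm, visit, arm-by-visit interaction, baseline weight and site. The primary contrast is the difference between arms at [one named visit]. Continuous secondary outcomes use the same model with their own baseline value. Two-hour glucose, which has one post-baseline value, is analysed by ANCOVA with its baseline value and site. Unadjusted t tests are supportive.*

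In addition:

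- Delete the reference to confounders.
- State whether the primary endpoint is continuous weight change or the proportion reaching 5% loss, and make Sample Size Calculation agree. If it is the proportion, use a logistic model at the named visit with arm, baseline weight and site.
- Add one sensitivity analysis in which dropouts return to baseline weight. It also covers people with no post-baseline weight, who contribute no outcome to the repeated-measures model.
- Ask for current weight at the contact with dropouts that is already planned.

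The cost is wording and a few lines of code in Stata or SPSS, both already named. No new visits are needed.

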#### Cost-Effectiveness

Two sets of outcomes are used to measure cost-effectiveness: cost-effectiveness analysis, which is the incremental cost per case of diabetes prevented, and cost-utility analysis, which is the incremental cost per QALY. The cost-effectiveness of the mHealth intervention is represented by the ratio of incremental cost to increment effectiveness. In addition, sensitivity analyses will be performed to examine effects of key parameters on cost-effectiveness ratios [36].

## Discussion

Mobile phone technology has been shown to have wide acceptance across various age groups and socioeconomic groups. It offers several opportunities for self-management as well as prevention of T2DM [40-42]. The mDiab study looks at the effect of combining various mHealth technologies that could all act as an effective tool for diabetes prevention in high-risk Asian Indians. The intervention is unique in that it is backed by evidence provided by the D-CLIP study [43]. The D-CLIP study was an RCT that compared an intervention group, which received 16 weekly sessions on lifestyle behavior change, nutrition, and physical activity, followed by 8 weeks of maintenance classes, with a control group that received standard of care. Individuals in the intervention arm who remained at high risk, that is, those with an HbA1c of >5.6% after 4 or more months in the program, received metformin, in addition to the lifestyle program. The goals for the individuals were set as weight loss of at least 7% and 150 min or more of moderate physical activity. In the mDiab intervention, however, we lowered the weight loss goal based on the learnings from the D-CLIP study as most Indians are not overtly obese. The D-CLIP results showed an almost 50% risk reduction in the obese population, and the numbers needed to treat were 6.8, which means that if 7 “high-risk cases” are given the intervention, one case of diabetes can be prevented [43].

On the basis of the D-CLIP results, the need to scale up diabetes prevention in India was felt, and mobile technology was thought of as a tool to introduce the intervention. This was the basis for the mDiab trial. Very few studies have been carried out in India to test the efficacy of mHealth technology in diabetes prevention. Ramachandran et al [44] studied the effect of SMS text messaging (short message service, SMS) in a high-risk population and showed that it is possible to decrease the incidence of diabetes with almost 10% difference between the groups by using a structured SMS text messaging intervention. However, their population sample was limited to working Indian men only. In another study that evaluated the impact of mobile SMS text messages on self-reported diabetes awareness and prevention behaviors among cell phone users in India, it was observed that the intervention group showed 15% improvement in their dietary and physical activity behaviors compared with the control group [45].

Globally, many studies have shown significant improvements in glycemic control using mobile phone technology. Hussein et al [46] showed that continuous and individualized support and interaction with a diabetes educator and a clinician through SMS text messages could decrease the HbA1c by 1.16% in individuals with type 2 diabetes. Studies using SMS technology, based on knowledge, attitude, practice, and self-efficacy and motivation, have shown improvement in glycemic control [47,48]. Some studies have also looked at secondary prevention of diabetes by enforcing self-management of lifestyle behavior, insulin therapy, medications, and physician visits [49,50]. The study by Browne et al [51] reported that younger adults are more susceptible to using eHealth services for diabetes self-management. This may be because younger adults were tech-savvy and found using eHealth self-management supports time-saving. The Diabetes MILES (Management and Impact for Long-term Empowerment and Success)—Australia study [52] reported that telehealth and eHealth are promising areas for diabetes management, especially to reach out to wider population groups.

In the context of rapid adoption of mobile technology [18] and the fast rise of the T2DM epidemic in LMICs such as India [1-3], mDiab is an RCT testing the effectiveness, cost-effectiveness, and sustainability of a culturally tailored mHealth diabetes prevention program for Asian Indians. If successful, mDiab can be used as a model for translational and implementation research on the use of mHealth technology for diabetes prevention. Indeed, the mDiab experience can be further expanded to the prevention of other noncommunicable diseases such as hypertension and cardiovascular diseases.

## Appendix

Multimedia Appendix 1 Summary of study measures.

Multimedia Appendix 2 “mDiab” overview of video lessons.

## Abbreviations

BMI: body mass index
CBG: capillary blood glucose
D-CLIP: Diabetes Community Lifestyle Improvement Program
FGDs: focus group discussions
IAMAI: Internet and Mobile Association of India
ICMR-INDIAB: Indian Council of Medical Research-India Diabetes
IDRS: Indian Diabetes Risk Score
IFG: impaired fasting glucose
IGT: impaired glucose tolerance
IMRB: Indian Market Research Bureau
LMICs: low- and middle-income countries
mHealth: mobile health
MPAQ: Madras Diabetes Research Foundation Physical Activity Questionnaire
QALY: quality-adjusted life-year
QOL: quality of life
RCT: randomized controlled trial
SMS: short message service
T2DM: type 2 diabetes mellitus
WHO: World Health Organization
